## 18.2 Terms of Reference

1. The Data and Safety Monitoring Committee for the PRET trials are charged with oversight of the quality of the data collected, and the safety and efficacy of the antibiotic approach proposed in the trial. The committee is guided by the principles set out in the National Eye Institute Guidelines for Data and Safety Monitoring of Clinical Trials.
2. As part of its responsibilities for oversight of safety issues, the Committee shall review reports on adverse events at each meeting. If any member expresses to the chair of the DSMC committee concerns for safety issues in the interim, the chair may request a meeting or telephone conference call of a quorum of the members. If the DSMC believes that there is evidence that warrants a change in the procedures of the clinical trial, the Committee will be responsible for drafting a report of their recommendations to the Executive Committee of PRET and to the IRBs as relevant of Johns Hopkins University, University of California at San Francisco, and London School of Hygiene and Tropical Medicine. If there is no concern, the Committee will also issue a report stating they have no concerns.
3. The DSMC shall meet together at least once per year, and more frequently by telephone if deemed necessary by the members or chair of the committee. The meeting shall be for the purposes of reviewing the accumulated data on the quality of the information collected, the safety of the trial procedures, and the efficacy of the treatment arms. The committee shall issue a summary report, which will be forwarded to the Executive Committee of PRET and each Institutional Review Board.
4. The locations of the trials are in rural Africa. Social, cultural, or political exigencies may arise that may affect the trial or call into question some of the protocols of the trial. The DSMC has accepted the responsibility to serve as a review body for such matters, if requested by members of the DSMC or members of the study team. The members of the DSMC may request a review by the full committee of any events arising from the study which, in the opinion of the committee member, is a serious issue or one in which a response to a government may be necessary. The Study Chair will arrange a conference call as expeditiously as possible with a quorum of members. For this purpose, a quorum is considered three of the four members, with the member from Africa required and the DSMC chair considered a member. The call must include the Study Principal Investigator and the relevant principal investigator from the country (or countries) involved. The committee will recommend a course of action to the Study Principal Investigator regarding any such events. If the study leadership does not concur with the DSMC's recommendation, it will be the responsibility of the study leadership and DSMC Chair to reach a mutually acceptable decision. A minority report will be issued from this group.

## 18.3 DSMC Key Responsibilities

The DSMC will be responsible for carrying out the following responsibilities:

- Reviewing and approving the trial protocol and plans for data and safety monitoring
- Assessing data quality, including completeness
- Monitoring recruitment and losses to follow-up
- Monitoring compliance with the treatment protocol by villages and investigators
- Monitoring evidence for intervention differences in the main outcomes
- Monitoring the safety of interventions (e.g., adverse events)
- Deciding whether to recommend that the trial continues as planned or whether treatment should be terminated in some treatment groups
- Reviewing proposed major modifications to the study prior to their implementation (e.g., increasing target sample size, dropping an arm based on other trial outcomes or toxicity results).
- Suggesting additional data analyses

## 18.4 DSMC Membership

Members of the DSMC are appointed by the Executive Committee of PRET. The DSMC is an independent multidisciplinary group consisting of the following four members:

[name]: Chair. Ophthalmologist  
 [name]: Pediatric Infectious disease  
 [name]: Ophthalmologist  
 [name]: Biostatistician and clinical trialist

The DSMC voting membership includes all four members mentioned above. Non-voting members include the members of the PRET Executive committee ([name], [name], [name], and [name]), and members of the PRET team as required: [name], [name], [name], [name], and [name].

### 18.4.1 Conflicts of Interest

The DSMC membership is restricted to individuals free of apparent significant conflicts of interest. The source of these conflicts may be financial, scientific or regulatory in nature. Thus, DSMC members may not be involved in PRET, have a vested interest in its outcome, have close personal or professional ties to a PRET investigator, or have financial investments in Pfizer. If at any time a DSMC member perceives that he/she or another member of the Committee has a potential conflict of interest, he/she is obligated to bring the issue to the attention of the full DSMC for open discussion and resolution. Any DSMC members who develop significant conflicts of interest during the course of trial should resign from the DSMC. The PRET Executive Committee will promptly appoint a replacement.

DSMC members will complete a conflict of interest disclosure form in advance of the first meeting. Competing interests should be disclosed by all DSMC members. The completed forms will be reviewed by the DSMC Chair. If a significant conflict of interest is noted, the DSMC Chair

will determine if that a member has a conflict of interest that would compromise their ability to serve on the DSMC. If he recommends resignation, the member will be replaced.

The DSMC membership is to be constituted for the duration of the PRET trials. Before the publication of PRET trial primary results, the DSMC members should not discuss issues from their involvement in the trial.

### **18.4.2 Relationships**

The DSMC is appointed by the Executive Committee of PRET and is advisory to the Executive Committee. The DSMC will not make decisions about the trials but rather advise the Executive Committee of PRET as to the data quality and safety of the interventions throughout the trial.

## **18.5 DSMC Meetings**

The DSMC will meet once per year, at the start of the project, and once per year thereafter when there is data to review. Additional DSMC teleconferences will be scheduled as the Chair recommends. The agenda will be prepared by the DSMC chair in consultation with the study investigators.

At least five days before the DSMC the Study Principal Investigator will send to the DSMC members a binder of study materials via Federal Express to allow the members' time to review the material before the meeting. The binders will include a set of data reporting tables, shown in Appendix 3. In keeping with confidentiality, the DSMC members will return the binder of materials to the Principal Investigator at the close of the meeting. The Study Principal Investigator and her team will be responsible for the preparation of meeting materials and all DSMC meeting arrangements.

Open sessions of the DSMC meeting may be attended by DSMC voting members, and the non-voting members, and key study team members from each of the clinical sites. Other members of the PRET study team may also be asked by the DSMC chair to attend.

Closed sessions of the DSMC will be attended only by the voting DSMC members, the Executive committee, and the three study statisticians. The closed session may be called when the DSMC reviews the safety and impact data unmasked as to random assignment. At the discretion of the DSMC chair, the committee can meet in Executive session with only the four voting members present to discuss issues and take formal votes as needed.

Minutes will be prepared by the Study Principal Investigator for the antibiotic trial, and the study project director for the surgery trial. Draft minutes will be combined and distributed to the DSMC chair for review and changes before distribution to the entire committee. The minutes shall summarize all recommendations.

Members must make every effort to attend DSMC meetings. If a member fails to make a meeting, it should be ensured that the member makes the next meeting. If a member fails to make the second meeting, the member will be replaced.

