## 8.5 Monitoring Mass Treatment Coverage

The census data that are obtained and updated yearly will be the primary tool used for monitoring mass treatment coverage. The programs that are built for data entry of the census data will have a report that will be generated that consists of Mass treatment lists for each community, organized as needed for each country (for example, mtaa in Tanzania, grappe in Niger, and village in The Gambia). These master lists are used to record observed treatment coverage for each resident of the community. The data entry of these lists is essential to monitoring coverage as the treatment is underway.

Features of the program will be tailored to each country needs: for example, in Tanzania, as data are entered on coverage, a report can be generated calculating the coverage of children ages to 9.5 years, and if coverage has not hit target, a further report can be generated listing, in random order, all households with at least one resident who has not been treated, and the residents missing treatment. These lists can be used to further guide mass treatment steps as described above, and the data from these reports entered to update coverage. At the end of mass treatment, each community resident should be accounted for as having been treated or not treated and the reason why.

After each community has completed its mass treatment, the full data set on treatment is sent to the principal investigator for each country within a week in order to monitor the success of the treatment team in reaching coverage targets. S/he will review the percent coverage of the community, and if it is over or under target, the reasons why in the file. This will be done within three weeks of mass treatment ending so that if necessary, the treatment team can be re-deployed to the community to improve coverage. If all residents are accounted for, and the resident did not meet treatment coverage targets, the principal investigator will discuss with the treatment team supervisor ways to improve coverage for the second or third rounds (perhaps different timing or working with other community health team members, for example).

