### **13.7 Quality Assurance for Field Trachoma Grading**

The images taken will be organized into folders for each examiner by visit. The folders will be sent to [name] for review and grading, as he is the standard to which all the field graders have been trained. He will grade each set of 50 digital images for quality of the image, using 2.5 magnification. The first observation is for grade-ability of the image. If more than 20% of the images are ungradeable for any one photographer, the clinical site will be notified, certification of photographer will be suspended and the photographer will have to be re-certified.

[name] will grade each gradable photograph with a clinical grade for trachoma, using the WHO simplified grading scheme. The grades will be transmitted to each study site data coordinating center, which will compare the grades with the grades assigned to the eyes in the field. Agreement will be assessed, and if agreement falls below 0.6 in any month, the reasons for disagreement will be discussed, and the set of photographs re-circulated to bring agreement to acceptable levels. If necessary, the survey will be interrupted while the study site lead investigator and the field grader re-grade photographs and undertake field work until agreement is re-established. Some of the disagreement could be due to differences between grading photographs and grading live eyes in the field, although we have shown very high concordance.

The quality assurance of grading in the field is a required report from each center that will be presented at six months to the executive committee for review and reported to the DSMC during their annual review.

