### 17.4 Clinical Centers: Niger, Tanzania, and The Gambia

The clinical centers have day to day responsibility for hiring and training staff, carrying out the trial in their country study sites, collection and transmittal of data, data management (discussed below), and data analyses for the data from their country site. Specific responsibilities include the following:

- Ensure the execution of the study at each site per protocol
- Coordinate with the Study Chairman's office in writing progress reports and budget accounting
- Maintain all ethical clearances for the study, including IRB renewals, and DSMC-related approvals for country specific activities
- In collaboration with JHU data coordination team, prepare all forms and documents necessary for fieldwork
- Participate in Standardization workshop; ensuring relevant country team members are present, trained, and certified. Each site must also train of team members for each data collection and mass treatment
- Arrange logistics and itineraries for traveling team members in country

- Purchase, maintain, and organize transport of all necessary study supplies to and within country
- Conduct data entry of data collected, ensure appropriate back up, and send data to data management team for each clinical site.
- Coordinate and oversee shipping of collected study samples per protocol and IATA regulations
- Coordinate and oversee sending of photographs per protocol to LSHTM for review
- Coordinate and oversee sending data as required to LSHTM for cost effectiveness component
- Coordinate and oversee sending of data as required to UCSF for modeling component
- Principal investigator for each clinical site will participate in Executive Committee Meetings, and teleconferences and DSMC meetings as needed.
- Prepare reports as required for quality assurance and monitoring purposes.
- Creation of manuscripts on data specific to each site, review through the Executive committee partners, and publication

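### The DSMC charter lets the Executive Committee, in whose meetings the site principal investigators take part, attend closed sessions that may show outcomes by arm

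*Protocol*

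**What the plan says.** Section 18.5 describes three kinds of DSMC session. Open sessions admit voting and non-voting members and key site staff. For the next kind, "Closed sessions of the DSMC will be attended only by the voting DSMC members, the Executive committee, and the three study statisticians". Their use is described as follows: "The closed session may be called when the DSMC reviews the safety and impact data unmasked as to random assignment". Third, at the chair's discretion, "the committee can meet in Executive session with only the four voting members present to discuss issues and take formal votes as needed".

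On timing, the same section says "The DSMC will meet once per year, at the start of the project, and once per year thereafter when there is data to review". Section 18.2 gives the purposes of the meeting as "reviewing the accumulated data on the quality of the information collected, the safety of the trial procedures, and the efficacy of the treatment arms", and Section 18.3 adds monitoring of between-arm differences in the main outcomes.

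Section 17.2 gives the Executive Committee a chair and three others, whose names are removed from the text. Section 17.4 says "Principal investigator for each clinical site will participate in Executive Committee Meetings", and in DSMC meetings when needed. Section 18.4 lists the Executive Committee as non-voting DSMC members, while Section 18.4.1 bars from membership anyone who has a part in PRET.

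**The concern.** A closed session normally separates those who see accumulating results by arm from those who run the trial. Here it excludes wider site staff but admits the trial's leadership. Three things are at stake:

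- **Coverage.** It is a randomised factor, delivered again in each later round with effort that the site investigator reviews.
- **Clinical trachoma.** It is part of the primary outcome and is graded in the field, by graders whose certification the site investigators must maintain.
- **Trial changes.** The DSMC only advises. The Executive Committee receives its recommendations and implements them.

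Someone who has seen which arm is ahead could, without intending it, push coverage harder in one arm, handle grader drift differently, or judge a proposed change in the light of the results.

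**Working it through.** No sample size, power or error rate is involved, so the check is to set the sections side by side.

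1. **Who attends.** Section 18.5 admits the Executive Committee to closed sessions by name. The only session without investigators is the discretionary one for discussion and votes.

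2. **What may be shown.** Section 18.5 ties the closed session to data unmasked by arm. Sections 18.2 and 18.3 make efficacy of the arms and between-arm differences part of the DSMC's work, so these data include comparative outcomes as well as safety.

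3. **Are site principal investigators among those attending?** Section 17.4 has each of them take part in Executive Committee meetings, and in DSMC meetings as needed. Because the names in Section 17.2 are removed, membership is a reasonable inference, not a stated fact.

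4. **What these investigators do in the trial.**
   - Section 8.5: the country principal investigator receives each community's treatment data, reviews coverage against target so that "the treatment team can be re-deployed to the community to improve coverage" if necessary, and discusses ways to improve later rounds.
   - Section 17.5.2: site investigators are responsible for keeping their graders certified.
   - Section 13.7: when agreement falls below 0.6, the survey may be interrupted while "the study site lead investigator and the field grader re-grade photographs".
   - Sections 17.2 and 18.4.2: the Executive Committee receives the DSMC's advice and acts on it.

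5. **Do they have these results already?** The stopping-rule report in Section 10.7, which goes to the site's senior principal investigator, gives one community's survey outcome and the resulting action. It does not compare arms. Section 4.3 says Niger has no stopping rule. Sections 17.5.1.1 to 17.5.1.3, however, require each coordinating center to analyse and supply data when co-investigators ask, with no restriction on results by arm. That is a second route to the same information.

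6. **How many looks.** Meeting dates are not given. Assume one meeting before treatment starts, with no outcome data, and then one each year. If the yearly meetings fall at months 12, 24 and 36 after first treatment, two precede the 36-month survey. If the cycle runs a little earlier, three do. Three is thus a ceiling for the yearly meetings, and Section 18.5 does not require an unmasked session at any of them.

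7. **Internal conflict.** Section 18.4 makes the Executive Committee non-voting DSMC members, and Section 18.4.1 excludes people involved in PRET from membership. The two cannot both hold as written unless the exclusion is meant for voting members only, which the text does not say.

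**The case against.** The strongest reply is that the charter keeps real safeguards and that the routes to bias are narrow. Only the four independent members vote. The chair can clear the room. Summary reports also go to each Institutional Review Board (Section 18.2). The PCR laboratories and the reference photograph grader are masked (Section 8.7). Re-grading is triggered by poor agreement with that masked reference and moves graders back towards it. Re-deployment is triggered by coverage data, and Sections 8.2 to 8.4 give each country its own rule for ending a treatment round. The trial is single-masked, so investigators can in any case know which community is in which arm.

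Much of this stands and limits the harm. It does not answer the point, because knowing a community's assignment is different from seeing accumulating outcomes compared by arm. Masked PCR protects the laboratory result, but not coverage effort, field grading or decisions on changes. The round-ending rules narrow discretion without eliminating it.

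A reader might infer more than the text supports:

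- **That investigators see unmasked results every year.** The yearly requirement applies to meetings; the closed session only may be called.
- **That the DSMC has lost its independence.** The voting rule, the voting-only session and reporting to the review boards argue against that.
- **That changing the attendance list is enough and needs no other arrangement.** The coordinating centers' duty to supply data would leave the second route open. Under Section 8.6 the Tanzania and Gambia statisticians themselves review the data for the stop/continue decisions, so not every existing statistician is detached from treatment decisions.

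**Conclusion.** The point holds as a weakness of governance. The charter permits the Executive Committee to be present when safety and impact data are reviewed by arm, and the site principal investigators who take part in that committee oversee coverage effort and grader certification while the trial runs. Independence is weakened, not removed.

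The exposure is two or at most three yearly meetings before the 36-month survey, potentially covering both randomised factors in all three countries. The resulting bias cannot be calculated from the protocol. It is likely smaller for infection, which is read by a masked laboratory, than for field-graded trachoma.

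The conclusion rests on two assumptions: that taking part in Executive Committee meetings carries access to the closed sessions, and that closed sessions will in practice be called, which the stated purposes of the meetings make likely.

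**What to change.** - **Section 18.5, attendance.** Limit any session showing outcomes by arm to the four voting members plus the statistician(s) presenting the tables. Those statisticians, not the Study Principal Investigator's team, prepare the by-arm tables and send them directly to the DSMC. Prefer a statistician who takes no part in the stop/continue determinations of Section 8.6. Where an existing one must serve, bar disclosure of by-arm outcomes to investigators.
- **Section 18.5, investigators.** The Executive Committee and site investigators attend open sessions with pooled data and receive written recommendations only.
- **Section 17.5.1.** State for all three coordinating centers that by-arm outcome analyses are not released to co-investigators before the 36-month data are complete, apart from the community-level stopping-rule reports.
- **Sections 18.4 and 18.4.1.** Reconcile the non-voting membership of the Executive Committee with the exclusion of people involved in PRET.

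The cost is charter and protocol wording, some reporting work reassigned among the existing statisticians, and the investigators' loss of interim sight of results by arm. No change to design, sample or data collection is needed.

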## 18.5.1 Protocol Changes and Ancillary Studies

The DSMC will meet in advance of the start of the trials. The DSMC is charged with reviewing and approving the protocols. The DSMC may review patient oral consent forms, but the institutional and country IRBS have primary responsibility for approval of these forms.

The DSMC will be informed in advance of major study protocol changes. DSMC concurrence will be sought on all substantive recommendations for changes prior to their implementation. Ancillary studies affecting the antibiotic trial in all countries will be brought forward to the DSMC for their information. The DSMC will review them for possible impact on the main trials. The DSMC will not make recommendations regarding whether the studies may or may not proceed, which is the province of the Executive committee.

